#### Inclusion and exclusion criteria

Inclusion criteria for the TAY are (1) having a psychological disorder, (2) being 15 to 25 years old, (3) being referred to one of the participating mental healthcare institutions. Exclusion criteria are (1) having insufficient knowledge of the Dutch language, (2) acute suicide risk, (3) currently meeting the criteria for a DSM-5 substance abuse, psychotic and/or bipolar disorder, (4) having an estimated IQ below 80, (5) unstable medication (i.e., the medication should be set before the start of the intervention and should remain stable during the intervention), (6) absence of TAY’s or parental permission (for adolescents below the age of 16).

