#### Sample size calculation

We calculated the sample size for a two-level multilevel analysis, using the Optimal Design program [64]. In accordance with our planned analyses, the first level represents the TAY and the second level represents the therapists. As most of the therapists either give the ACT your way or the TAU intervention, we calculated the sample size as for a cluster RCT in which the therapists represent the clusters. Within our sample size calculation, we used a cluster size (i.e., the expected number of therapists) of 70, as we expect that in both conditions approximately 35 therapists will be carrying out either the ACT your way or TAU intervention. In addition, we used an ICC of 0.05 as this is the average ICC reported in meta-analyses of therapist effects in psychological intervention research [65]. Furthermore, the effect size is based on a meta-analysis in which 39 RCT’s were included that investigated the efficacy of ACT, including 1,821 adults with various mental disorders [21]. We based the effect-size on this meta-analysis as, to our knowledge, this is the most recent meta-analysis examining the effects of ACT transdiagnostically. When ACT was compared to TAU a medium effect was found (Hedges g = 0.64), when ACT was compared to CBT a small effect was found (Hedges g = 0.32). In this study ACT will be compared to TAU, presuming a medium effect around 0.64. However, since we want to be conservative and expect that, at least with some of the participants, CBT will be used in TAU as well, an effect size of 0.50 was included in the sample size calculation. Hence, with a cluster size of 70, an effect size of 0.50, an ICC of 0.05, an α of 0.05 and a power of 0.8, a sample size of 140 (i.e., on average two TAY per therapist, and 70 TAY per condition) is assumed.

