### Study design and procedure

The study is designed as a multi-center, randomized controlled trial (RCT). Data will be collected in 14 Dutch and Belgian mental healthcare institutions. Within each institution, TAY meeting the inclusion/exclusion criteria, their parents/caregivers and their therapists will be asked to participate in the study. Parents/caregivers of adolescents younger than 16 will be directly involved in the study. TAY aged 16 and older will be asked first for permission to contact their parents/caregivers. If they agree, their parents/caregivers will be asked to participate in the study as well. Before enrolling in the study, written informed consent from TAY and parents/caregivers/legal representatives (for adolescents younger than 16) will be obtained. If parents/caregivers and therapists agree to participate, they will be asked for their own written informed consent as well.

In total, six multiple informant (TAY, parents/caregivers, therapist) assessments will be conducted: at baseline (T0), after 3 sessions (T1), after 6 sessions (T2), after 9 sessions (T3), at post-intervention (T4) and at 6-month follow-up (T5). Assessments will include diagnostic interviews (at T0, T4 and T5) and questionnaires (at T0 to T5). The assessments will be conducted by research assistants working at the participating institutions (e.g., master students and psychologists). Research assistants will be trained in administering the diagnostic interview and questionnaires. The TAY will receive a 30 euro gift card as a reward (5 euros per assessment). After the baseline assessment (T0), TAY will be randomly assigned to either the ACT your way or TAU condition using a computer generated block design. At each institution, five participants will be randomly allocated to the ACT your way condition and five participants will be randomly allocated to the TAU condition (blocksize = 10). See Fig. 1 for an overview of the study design.

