#### Effectiveness

The effect of the intervention on the primary (i.e., psychological flexibility and number of DSM-5 diagnoses) and secondary outcomes (i.e., presence of the primary DSM-5 diagnosis, psychopathology, personality problems, global functioning, individual and societal functioning, quality of life, stress, treatment satisfaction, drop-out and therapeutic alliance) will be evaluated using a two-level multilevel analysis in Mplus [115]. Specifically, we will investigate, if condition (i.e., ACT or TAU) predicts the post-intervention (T4) and 6-month follow-up (T5) levels of our primary and secondary outcomes, while controlling for the baseline levels of the concerning outcomes. We will perform a two-level multilevel analysis as we expect that TAY will be nested within therapists. Hence, the first level will represent the TAY and the second level will represent the therapists. We do not expect variance at the measurement level, as the analyses will be performed separately for the post-intervention and 6-month follow-up assessments. Although we expect that therapists will be nested within institutions, we will not include a third level as the number of institutions in our study is too small (i.e., 14 institutions). Instead, in all analyses, we will add dummies representing the mental healthcare institutions.

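### The own-baseline rule is empty for presence of the primary diagnosis and cannot be applied to three other secondary outcomes; under a logistic model, the institution dummies would add to overstatement of a non-null odds ratio

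*Protocol article*

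**What the plan says.** In the protocol article, Data analysis, Effectiveness, every primary and secondary outcome "will be evaluated using a two-level multilevel analysis in Mplus", with participants at level 1 and therapists at level 2. The list includes presence of the primary DSM-5 diagnosis and drop-out. Condition predicts the T4 and T5 levels "while controlling for the baseline levels of the concerning outcomes". Institutions are not a third level: "Instead, in all analyses, we will add dummies representing the mental healthcare institutions".

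Four other places bear on this rule:

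- Inclusion and exclusion criteria: "Inclusion criteria for the TAY are (1) having a psychological disorder".
- Study design and procedure: at each of 14 institutions, "five participants will be randomly allocated to the ACT your way condition and five participants will be randomly allocated to the TAU condition".
- Table 1: drop-out is recorded at T4 only and therapeutic alliance at T1 to T4. Treatment satisfaction is marked at T4 in the table and placed at T5 in the text. None of the three has a T0 value.
- Table 1 and Primary outcomes: the number of DSM-5 diagnoses is measured at T0, T4 and T5 with the SCID-5-Junior.

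The article gives no link function for the binary outcomes and no expected rate for the primary-diagnosis outcome.

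**The concern.** The rule is written as if every outcome were continuous and measured at baseline. Several listed secondary outcomes are not.

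First, a covariate that takes one value for all participants is indistinguishable from the intercept. Presence of the primary diagnosis would then be analysed with no prognostic adjustment from this rule, although a usable T0 covariate is on file. For three other outcomes the rule asks for a variable that does not exist.

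Second, a set of stratum dummies is harmless in a linear model. In a maximum-likelihood logistic model with few participants per stratum, it pushes a non-null log odds ratio away from zero. Ten participants per institution is few enough for this to show. At stake is the size of the odds ratios reported for two outcomes on which the article predicts a benefit.

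**Working it through.** **1. The plan's own figure.** Inputs from Sample size calculation: "with a cluster size of 70, an effect size of 0.50" and "an ICC of 0.05, an α of 0.05 and a power of 0.8", with "on average two TAY per therapist, and 70 TAY per condition". The 70 is the number of therapists, J; n = 2 participants each.

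- Var = 4 × (ICC + (1 − ICC)/n)/J = 4 × (0.05 + 0.95/2)/70 = 0.030, so SE = 0.173.
- Noncentrality = 0.50/0.173 = 2.89. With 68 degrees of freedom and a two-sided 5% test (sidedness is assumed), power is 0.812.

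The 140 reproduces. It rests on a standardised mean difference, so nothing below affects it.

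**2. Baseline rule against the measurement schedule.**

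| Outcome | T0 value | Effect of the rule |
|---|---|---|
| Presence of primary diagnosis | Measured, but essentially always present given the entry criterion | Covariate is constant and drops out |
| Drop-out | None | Cannot be applied |
| Treatment satisfaction | None | Cannot be applied |
| Therapeutic alliance | None | Cannot be applied |
| Number of diagnoses | Measured at T0; a count | Works as intended |

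The constancy could fail only if an entry diagnosis is not confirmed by the SCID-5-Junior at T0.

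**3. Institution dummies under an assumed logit link.** 14 institutions need 13 dummies. With 140/14 = 10 participants each (5:5) and strata of size m, the expected inflation is near m/(m − 1) = 10/9, or about 11%. Simulations with 200 institutions gave +11% to +12%, which agrees.

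Simulations of 14 × 10 participants, 1,500 trials per setting, at assumed event rates (ACT your way vs TAU):

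| Model | Rates | True log OR | With dummies | Without dummies |
|---|---|---|---|---|
| Single-level | 30% vs 50% | −0.847 | −0.956 (+12.8%) | −0.861 (+1.7%) |
| Single-level | 25% vs 50% | −1.099 | −1.249 (+13.7%) | −1.123 (+2.2%) |
| Two-level, therapist ICC 0.05 | 30% vs 50% | −0.847 | −0.963 (+13.6%) | −0.906 (+6.9%) |
| Two-level, therapist ICC 0.05 | 25% vs 50% | −1.099 | −1.237 (+12.6%) | −1.160 (+5.6%) |

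- Range with dummies, single-level: +9.5% to +14.1% over all rates tried without institution variation; +12.9% to +18.9% with an institution SD of 0.5 on the logit scale.
- Share due to the dummies: about 10 to 11% in the single-level fit without institution variation. In the two-level fit, 13.6 − 6.9 = 6.7 and 12.6 − 5.6 = 7.0 points.
- A second, shorter two-level run gave totals of +12.6%, +11.0% and, at 20% vs 41%, +8.7%. The dummies accounted for 7.7, 7.0 and 6.6 points.
- Relative to noise: (0.963 − 0.847)/0.42 and (1.237 − 1.099)/0.45, about 0.3 of the estimate's SD.
- No effect (40% in both arms, two-level): no bias. The likelihood-ratio test rejected in 6.6% of trials with dummies and 4.3% without.
- Conditional logistic regression by institution (single-level): 0.99 to 1.02 times the true log odds ratio.

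As an illustration, at 1.13 times the log odds ratio a true 0.50 is reported as 0.50^1.13 = 0.46.

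**4. Sparse institutions, for drop-out.** The Background cites 20.6% (pilot) and 41 to 57% (an earlier CBT trial). These are not planning values.

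- At 20.6% throughout: 140 × 0.206 = 29 events for about 15 parameters (intercept, condition, 13 dummies). Expected all-or-none institutions: 14 × (0.794^10 + 0.206^10) = 1.4.
- At 20.6% vs 41%, an institution has no drop-outs with probability 0.794^5 × 0.59^5 = 0.0226. At least one such institution: 1 − (1 − 0.0226)^14 = 27%.
- At 20.6% vs 57%: 0.794^5 × 0.43^5 = 0.0046, giving 6%.

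**The case against.** The strongest reply is that nothing fails. A reader might infer that the model breaks down for binary outcomes, and the documents do not support that. A constant covariate drops out without biasing the treatment effect, and a missing baseline only means there is nothing to adjust for. An all-or-none institution has no finite dummy estimate, but it carries no information on the treatment effect, so the log odds ratio stays finite. Conditional logistic regression sets aside the same institutions, so sparsity alone is no argument for it. All of this stands.

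Next, the article names no link, estimator or event rates, and a condensed article may leave these to the full plan. It does not even say that drop-out is coded yes or no. A linear probability model would not show the inflation. This also stands: the second point is conditional, and the missing link is not itself a fault.

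It is equally tempting to attribute the whole 13% to the dummies. In the two-level model that the article specifies, about half is present without them.

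The dummies are also legitimate in principle, because allocation is balanced within institution, and the alternatives give up the therapist random effect around which the analysis is built. That is a genuine trade-off. Finally, diagnostic characteristics that differ between arms at baseline enter all analyses as covariates, so T0 information is not ignored altogether. It enters only when an imbalance happens to appear, which does not replace a covariate fixed in advance.

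**Conclusion.** The point holds in limited form, for secondary outcomes only.

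From the documents alone: own-baseline adjustment does nothing for presence of the primary diagnosis, given that the T0 diagnosis follows from the entry criterion, and it cannot be carried out for drop-out, treatment satisfaction or therapeutic alliance. The consequence is a lost chance of adjustment and an unworkable instruction, not bias.

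On assumption: if the binary outcomes are fitted by maximum-likelihood logistic regression with 13 dummies over about 10 participants each, a non-null log odds ratio is overstated by roughly 10 to 15% in total. Individual settings ran from about 9% to 19%. The dummies themselves contribute about 7 points in the two-level model. Under no effect there is no bias and only a modest excess of rejections. The shift is about 0.3 of the estimate's SD, so it matters for the reported size of an effect more than for whether one is declared. The primary outcomes and the sample size of 140 are unaffected.

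**What to change.** 1. Limit the baseline rule to outcomes with a T0 value that varies. State that drop-out, treatment satisfaction and therapeutic alliance are analysed without an own-baseline covariate.
2. For presence of the primary diagnosis, replace its own baseline with the T0 number of DSM-5 diagnoses. It is already collected, so this costs nothing.
3. For presence of the primary diagnosis, and for drop-out if analysed as yes/no by logistic regression, either exempt the analysis from the dummy rule or add a sensitivity analysis. That analysis could be conditional logistic regression stratified by institution or a Mantel-Haenszel risk difference by institution. Both still respect the balanced allocation within institution. Handle therapist clustering by robust errors.
4. Keep the dummies for continuous outcomes.

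The cost is wording and one extra analysis for each of two secondary outcomes. The downside is losing the therapist random effect in that analysis. Therapists sit within institutions, so check beforehand that the software can compute therapist-level robust errors for the conditional model; some routines cluster only at the stratum level, which here leaves 14 clusters. The Mantel-Haenszel risk difference avoids that difficulty and also retains the all-or-none institutions, but it does not by itself take the T0 covariate.

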#### Cost-effectiveness

Cost-effectiveness analysis will be conducted by comparing costs and effects between the ACT your way and TAU condition. The economic evaluation will be executed in accordance with the international guidelines [116]. The cost-effectiveness analyses will be done separately from the perspective of mental health and society over a period of 6 months. The effects of societal costs will be expressed in years to live, corrected for quality of life (QALYs). The costs of ACT you way versus TAU will be expressed in incremental costs per QALY and incremental costs per TAY with the number of diagnoses.

#### Moderation and mediation

To examine if intervention effects are moderated by demographic characteristics (i.e., gender, age, education level and ethnicity), type and severity of problems, psychopathology of parents/caregivers, treatment expectancy and previous treatments, interaction terms will be added to the multilevel model [115].

To investigate if the intervention effects on the primary and secondary outcomes are mediated by psychological flexibility (only for outcomes other than psychological flexibility), emotional regulation, self-compassion, autonomy, perfectionism, self-esteem and group-cohesion at T1, T2 and/or T3, we will perform path-analyses in Mplus [115]. In the analyses we will use a bootstrap procedure and control for the dependency in our data with the “type is complex” and “ML robust estimator” commands.

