### Study conditions

#### ACT your way

ACT your way consists of 12 weekly sessions, that can be carried out both individually as in groups. The therapists at the clinical institutions decide if they carry out ACT your way individually or in a group. There is a guide for therapists [66], a workbook for TAY [67] and a website with additional videos, mindfulness exercises and information for TAY. Each session lasts either 120 (group therapy) or 60 (individual therapy) minutes and has a fixed format in which psychoeducation, mindfulness exercises, metaphors and experiential exercises are carried out. The 12 sessions are divided into four blocks, each comprising of three sessions. The first block focusses on values (i.e., desires regarding development, identity, and autonomy). The second block focusses on the six core processes of psychological inflexibility (i.e., experiential avoidance, cognitive fusion, dominance of conceptualized past and feared future, attached to the conceptualised self, lack of values, and inaction). The third block focuses on acquiring skills based on the six core processes of psychological flexibility (i.e., acceptance, cognitive defusion, contact with the present moment, self as context, values, and committed action). With these skills, TAY can consciously choose behaviours that fit their chosen values. The fourth block focusses on continuing and strengthening TAY’s psychological flexibility and preparing the TAY for possible relapses in the future. In this study, ACT your way will be carried out in a face-to-face format by therapists working at the participating mental healthcare institutions. The therapists will be trained in using ACT your way (i.e., a two day training in the basics of ACT and a two day training in ACT your way specifically). Moreover, during the course of the study, the therapists will be supervised by an ACT expert.

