#### Treatment as usual

TAU can also be carried out both individually as in groups and will consist of a broad range of different psychological interventions, such as CBT, parent counselling, emotion regulation training, running therapy, or psychodynamic therapy. Therapists of the participating mental health care institutions decide what intervention(s) are most suitable to be carried out as TAU. We expect that in most cases, similar to ACT your way, TAU will also consist of weekly sessions. However, in the few cases that this is not possible, it is also acceptable to have bi-weekly sessions within TAU. If TAU is carried out bi-weekly, the T1, T2, T3 and T4 will take place after 2, 4, 6 and 8 sessions, respectively. We choose this option as then both in the ACT your way as TAU condition, the assessments will take place approximately around the same time.

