The Autonomy Adolescent Questionnaire (AAQ) [103] will be used to measure *autonomy* at T0, T2, T4 and T5. The AAQ divides autonomy into three main categories: attitudinal, emotional and functional autonomy. The AAQ contains 18 items that are rated on a 5-point Likert scale ranging from 0 = “*not all true for me*” to 4 = “*totally true for me*”. The factor structure, convergent validity and divergent validity of the AAQ has been supported in earlier research [103].

*Perfectionism* will be measured with the Frost Multidimensional Perfectionism Scale (FMPS) [104] at T0, T2, T4 and T5. The FMPS consists of 35 questions that are rated on a 5-point Likert scale ranging from 0 = “*strongly disagree*” to 4 = “*strongly agree*”. The reliability and validity of the FMPS is established in earlier studies [104]. In the current study, we only use the subscales: personal standards, organization, concern over mistakes and doubt about actions, containing 26 questions in total. To reduce the burden for TAY, we excluded the subscales: parent expectations and parental criticism as we believe that how TAY view their parents’ expectations and criticism will not be targeted within the intervention.

*Self-esteem* will be measured with the Rosenberg Self-Esteem Scale (RSES) [105, 106] at T0, T2, T4 and T5. The RSES contains 10 questions that are rated on a 4-point Likert scale ranging from 0 = “*totally agree*” to 3 = “*totally disagree*”. Earlier research demonstrated the validity and test- retest reliability of the Dutch RSES [105].

For TAY who receive ACT your way or TAU in a group, *group cohesion* will be measured with the Group Climate Questionnaire-Short (GCQ-S) [107] at T1, T2, T3 and T4. The GCQ-S was revised for TAY. The questionnaire contains three subscales (i.e., Engagement, Conflict and Avoidance) and 12 items that are answered on a 7-point scale ranging from “*totally disagree*” to “*totally agree*”. The reliability and validity of the GCQ-S has been demonstrated as good [108, 109].

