The presented study design has some potential challenges that could turn into limitations if not handled properly. Hence, for each potential challenge, a solution to overcome this challenge will be discussed. First, in the current study, ACT your way will be carried out both in an individual as in a group format, making it more difficult to isolate intervention effects from treatment modality effects. We decided to carry out ACT your way both individually as in groups, as both treatment modalities have their own potential advantages. For instance, group interventions might provide more opportunities for normalization, positive peer modeling and social support, whereas within individual interventions, therapists can more easily adapt exercises and subjects to the specific wishes and needs of each client. To isolate intervention from treatment modality effects, we will perform additional analyses in which we explore possible differences between both treatment modalities (see Method section). Second, the TAU condition might be heterogeneous in content and duration, which makes it challenging to compare the effects of ACT your way with the effects of TAU. To address this challenge, we will ask all therapists in the TAU condition to write down the content and duration of each session. Subsequently, we will investigate if there are differences in duration between ACT your way and TAU. If there are differences, the duration of treatment will be added as covariate in all analyses. Third, recruiting a sample of 140 TAY in 24 months could be challenging. To reach this sample size, we will cooperate with fourteen mental health care institutions in the Netherlands and Belgium. Moreover, to promote participation, we will give TAY a 30 euro giftcard as a reward and only use online questionnaires that TAY, parents/caregivers and therapists can easily fill out at home. Last, non-response and/or drop-out can also be a potential challenge. To minimize non-response, we built a website, including a system that automatically sends research assistants weekly updates via mail, that helps research assistants to monitor the assessment progress. At the website and in the weekly updates, research assistants can easily see which questionnaires are filled out or not and which ones are planned. With the help of this website and automatic mailing system, researchers can directly react to non-response and increase the response rate of the study. To minimize measurement drop-out, we will motivate TAY to continue participating by sending them thank you emails and newsletters and handing out a 5 euro gift card after each assessment. Moreover, when participants drop out of treatment, we will still ask them to fill out the post-intervention and follow-up assessments. Furthermore, to avoid potential bias due to drop-out, all analyses will be carried out according to the intention to treat principle.

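### The mediation plan covers treatment drop-out as an outcome, but participants who stop before T1 (or before T2, for four of seven mediators) have no mediator value between randomisation and the event

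*Protocol article*

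**What the plan says.** **Scope.** The Moderation and mediation section plans path analyses "To investigate if the intervention effects on the primary and secondary outcomes are mediated by psychological flexibility" and by "emotional regulation, self-compassion, autonomy, perfectionism, self-esteem and group-cohesion at T1, T2 and/or T3". It writes one exemption: psychological flexibility is not tested as a mediator of itself. The Effectiveness section's list of secondary outcomes ends with "quality of life, stress, treatment satisfaction, drop-out and therapeutic alliance". Table 1 and the first study aim also class drop-out as a secondary outcome.

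**Timing.** Study design and procedure places the in-treatment assessments "after 3 sessions (T1), after 6 sessions (T2), after 9 sessions (T3"). For bi-weekly control treatment, the Treatment as usual section says: "If TAU is carried out bi-weekly, the T1, T2, T3 and T4 will take place after 2, 4, 6 and 8 sessions, respectively". On length, "ACT your way consists of 12 weekly sessions".

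**What is measured when.** Psychological flexibility and emotion regulation (ERSQ) have short forms at T1 and T3. Group cohesion is measured from T1, in group treatment only. Self-esteem "will be measured with the Rosenberg Self-Esteem Scale (RSES) [105, 106] at T0, T2, T4 and T5", and self-compassion, autonomy, perfectionism and the FEEL-KJ follow the same schedule. Within the T1 to T3 window these have T2 alone.

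**After drop-out.** The Discussion says that "when participants drop out of treatment, we will still ask them to fill out the post-intervention and follow-up assessments". It does not mention T1 to T3. The Secondary outcomes section has the therapist record the date of drop-out and the number of sessions attended.

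**The concern.** A mediator has to lie between randomisation and the outcome. For outcomes measured at T4 or T5, a T1 to T3 score does. Drop-out is different: it can happen at any point in treatment, including before the first mediator is taken. Whether a usable score exists then depends on the outcome itself.

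The first study aim predicts less drop-out with ACT your way, so a reader may well want to know the mechanism. If the prediction is right, more early leavers come from TAU. Both the path from condition to mediator and the path from mediator to drop-out would then be affected differently by arm. A mechanism reported for lower drop-out could reflect who stayed long enough to be measured.

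**Working it through.** **Step 1: which values can serve as a mediator of drop-out.**

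- T0 precedes randomisation, so it cannot carry an effect of condition.
- T4 and T5, where a participant who stopped completes them, come after the event.
- T1 to T3 qualify only if taken before the participant stops. A T1 to T3 score collected on a calendar date after drop-out would also follow the event.

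The consequence by mediator:

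| Mediator | Measured in the T1–T3 window | No pre-event value if the participant stops before |
|---|---|---|
| Psychological flexibility | T1, T2, T3 | T1 |
| Emotion regulation (ERSQ) | T1, T2, T3 | T1 |
| Group cohesion (group treatment only) | T1, T2, T3 | T1 |
| Self-compassion | T2 | T2 |
| Autonomy | T2 | T2 |
| Perfectionism | T2 | T2 |
| Self-esteem | T2 | T2 |

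Four of seven mediators therefore depend on T2. The FEEL-KJ is also T2-only, but it is a second instrument for emotion regulation, not an eighth mediator. T1 and T2 fall after 3 and 6 sessions in weekly treatment, and after 2 and 4 in bi-weekly TAU.

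**Step 2: what the model can do with these cases.** Listwise deletion removes them, so the analysis conditions on having survived part of the outcome. A full-information maximum likelihood fit can keep them, but they bring no mediator information from before the event. Missing-at-random is then doubtful, because drop-out itself decides whether the mediator is measured.

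**Step 3: size.** The plan states no number or timing of drop-outs, so there is no figure of its own to reproduce on this point. The one planned figure used is 70 per condition, and it reproduces. With J = 70 therapists, m = 2 participants each, d = 0.50 and ICC = 0.05, the non-centrality is J·d²/(4·(ICC + (1 − ICC)/m)) = 17.5/2.1 = 8.33. On 1 and 68 degrees of freedom (two-sided 5% assumed) the power is 0.812.

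Expected events = 70·p(ACT) + 70·p(TAU). The rates come from the background section: 20.6% in the ACT your way pilot and 41 to 57% in a CBT trial. Applying them here is an assumption.

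- 20.6% in both arms: 14.4 + 14.4 = 28.8
- 20.6% and 41%: 14.4 + 28.7 = 43.1
- 20.6% and 57%: 14.4 + 39.9 = 54.3

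Timing is also assumed. The shares of drop-outs before T1 and T2 are 10% and 30% (late), 25% and 50% (uniform: 3/12 and 6/12 sessions), and 50% and 75% (front-loaded).

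| Events | Before T1: late / uniform / front-loaded | Before T2: late / uniform / front-loaded |
|---|---|---|
| 28.8 | 2.9 / 7.2 / 14.4 | 8.7 / 14.4 / 21.6 |
| 43.1 | 4.3 / 10.8 / 21.6 | 12.9 / 21.6 / 32.3 |
| 54.3 | 5.4 / 13.6 / 27.2 | 16.3 / 27.2 / 40.7 |

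**The case against.** The best defence is that nobody meant to mediate drop-out. The mediation aim names only the number of diagnoses and quality of life as outcomes. The first aim explains the expected drop-out difference by fit with participants' needs, which is not a listed mediator. The Mediators section limits psychological flexibility to some outcomes, and detail may sit in an analysis plan that is not shown. This makes an oversight plausible but does not change the stated scope. The outcomes in the mediation aim are given as examples, the narrower wording covers one mediator of seven, and the analysis section writes an exemption for another case but none for drop-out.

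A second defence is that the plan leaves the time point open, so T1 alone could be used. That helps the three mediators measured at T1, which are much less affected. It does nothing for the four with T2 only, or for anyone who stops before T1.

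Three stronger readings are tempting, and the documents support none of them:

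- **That a known, large share of events is lost.** No drop-out timing is given. The 41 to 57% comes from a CBT trial in 12 to 21 year olds, whereas TAU here is a broad mix of treatments.
- **That these participants are necessarily left out.** The section does not state listwise deletion, and full-information maximum likelihood could retain them.
- **That the missingness is shown to be not at random.** Drop-out, its date and the sessions attended are recorded, so dependence on drop-out does not prove it. Missing-at-random is doubtful, not refuted.

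**Conclusion.** The point holds in a limited form. As written, the plan commits to a mediation analysis of treatment drop-out that the assessment schedule cannot support for early leavers. That part follows from the text and needs no assumption about rates.

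Its size does depend on assumptions. Over the rates and timings above, about 3 to 27 of 29 to 54 events precede T1 (10 to 50%), and about 9 to 41 precede T2 (30 to 75%). These ranges are illustrations. They use 70 per arm, rates borrowed from other studies and three invented timing patterns.

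The reach is narrow: one secondary outcome within an explanatory aim. Mediation of outcomes measured at T4 or T5, the primary outcomes, the between-arm comparison of drop-out and the sample size are not touched by this argument.

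**What to change.** In the Moderation and mediation section, add one sentence that exempts treatment drop-out from the mediation outcomes, next to the existing exemption for psychological flexibility as its own mediator.

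If the question is to be kept, restrict it to an analysis labelled as an exploratory landmark analysis:

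- population: participants still in treatment at T1;
- mediators: only those measured at T1;
- outcome: drop-out after T1, dated from the therapist's record of date and number of sessions;
- interpretation: no claim about the total effect of condition on drop-out.

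No new data are needed. The cost is that one exploratory mediation question is dropped or narrowed.
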